#### School staff

Across both intervention and BAU schools, classroom teachers, school leaders (principals, assistant principals, leading teachers) wellbeing staff and education support staff (i.e., non-teaching staff who provide student, teaching and/or school support) will be invited to participate in the study by completing an online survey at multiple timepoints (see Fig. 1 and Table 2). Staff within these roles will receive an email from their principal inviting them to complete an online survey. The email at T1 will include a link to complete a web-based consent form, including the relevant plain language statement, before completing the survey.

#### Years 2 and 4 classroom teachers and parents/carers

Across both intervention and BAU schools, parents/carers of students from years 2 and 4 (ages 7–8 and 9–10) will receive an email from the principal (T2) inviting them to (a) consent to information being collected about their child by the classroom teacher and (b) complete an online survey at two timepoints (see Fig. 1). Parents/carers must be the primary caregiver of a student from one of the selected year levels. Classroom teachers from years 2 and 4 will subsequently receive an email from the principal (T3) inviting them to complete the Strengths and Difficulties Questionnaire [52] on each child in their class for whom parental or carer consent has been obtained (see Fig. 1  and Table 2). Parents/carers and teachers will be asked to complete an online consent form, including the relevant plain language statement before completing the survey (Table 1).

**Table 1 Tab1:** Summary of participant groups and projected number of participants in each group

Participant group		Number of participants	
		Intervention schools	BAU schools
MHWC and other trainees	MHWC	16 (1 per school)	–
	Training participants	48 (3 per school)	–
School staff	Classroom teachers^a^	192 (12 per school)	192 (12 per school)
	Education Support Staff	32–48 (at least 2 per school)	32–48 (at least 2 per school)
	School leadership (principal, APs, leading teachers, wellbeing)	32–48 (at least 2 per school)	32–48 (at least 2 per schools)
Parents/carers	Parents/carers from years 2 and 4	496 (31 per school)	496 (31 per school)
Year 2 / Year 4 classroom teachers	Classroom teachers from years 2 and 4	64 (2 classrooms per year level per school)	64 (2 classrooms per year level per school)

^a^ Primary outcome will be measured within this participant group. See further details under Sample Size Calculation

### Procedure

#### Intervention

The intervention will consist of the MHWC role and the MHWC training program.

#### Mental Health and wellbeing coordinator (MHWC) role

For each intervention school, a MHWC will be employed and funded a full-time equivalency (FTE; outlined below). To be recruited for this role the MHWC should have a teaching qualification and registration with the Victorian Institute of Teaching. Once recruited the MHWC will:
Receive evidence-based training around supporting the mental health needs of primary school students;Embed evidence-based training and professional development (Tier 1 practices & frameworks) across the school and build the capability of teaching and education support staff to better identify and support students with mental health issues;Be a significant contributor to the school’s wellbeing team;Support the referral pathway for students identified as requiring further assessment and intervention within the school or to external community-based services (the MHWC role will not involve providing 1:1 counselling support to students);Work proactively with regional staff (i.e., psychologists, speech and language therapists, social workers), school wellbeing and leadership teams, and other health professionals (community-based psychologists, paediatricians, GPs, other allied health) to engage appropriate mental health support such as assessment, counselling, classroom based adjustments;Connect wellbeing initiatives across the school and be responsible for implementing whole school approaches to mental health and wellbeing, including the social and emotional learning curriculum.

MHWC full time equivalency (FTE) allocation will be determined based on number of student enrolments at each school using the following scale: 0–149 students = 0.4 FTE, 150–299 students = 0.6 FTE, 300–449 students = 0.8 FTE, > 449 students = 1.0 FTE. An additional loading will be provided for MHWCs working in regional and rural schools.

#### MHWC training program

The MHWC will participate in a purpose designed training program, delivered by the research team, to increase their knowledge, skills, and attitudes to effectively focus on building the capacity of the whole school, working with individual teachers and the whole staff cohort. To promote whole school upskilling, encourage staff buy-in, and maximise the chance of sustainably embedding the MHWC model in the broader school setting, leaders at each intervention school will nominate three additional staff members to attend components of the MHWC training (training participants). All MHWCs will receive an explanation of the research component at the induction session by the training delivery lead and complete a plain language statement. Nominated training participants must be members of school leadership (i.e., principal, assistant principal, leading teacher), wellbeing staff, or a teacher (classroom) at an intervention school. Administrative staff will be excluded from the MHWC or training participant groups.

The intervention comprises an induction session followed by three core modules: Mental Health Literacy; Supporting Need; and Building Capacity attended by MHWCs and nominated additional school staff. MHWCs will also attend Communities of Practice sessions which will involve a selected expert for each session (Fig. 2). The content of the core modules will focus on the following broad areas:
Mental health and wellbeing as a continuum, including behavioural, social emotional and learning indicators;Risk and protective factors for mental health issues and promoting wellbeing;Engaging parents and carers and supporting school staff in conversations with parents and carers about student mental health and wellbeing;Building and maintaining effective relationships with service providers;Understanding the referral pathways within the school system and into the community;Evidence-based prevention and promotion approaches and programs and evaluating their effectiveness and fit for purpose in the school context.

**Fig. 2 Fig2:**
[figure not shown]
Content and structure of the training program for MHWCs

The instruction will use a problem/task centred approach informed by Merrill’s first principles of instruction [53]. These principles work on the basis that learning is promoted when: learners acquire knowledge in the context of real-world problems; existing knowledge is activated as a foundation for new knowledge; new knowledge is demonstrated to the learner, applied by the learner, and integrated into the learner’s world. MHWCs and other school participants will practice applying their knowledge through case studies, role-plays, and case studies and examples from their school context. Outputs of the training include a mental health and wellbeing profile and plan, and care pathway mapping based on each participant’s individual school context and circumstances.

Induction and the three core modules will be delivered over an intensive 3-day training program via a synchronous online environment, using teleconference technology to facilitate the building of professional networks and communities of practice between schools. In addition, asynchronous learning will include, videos, content-based activities, pre-reading, skills and knowledge checks, completion of online modules from other providers (as pre-requisites to cover basic concepts and engage with potential resources for staff professional development) and reviewing previously covered material to consolidate learning. Communities of practice and skills practice ‘on-the-job’ will also form an integral part of the learning approach and will continue as part of the model once the core training modules are delivered.

#### Comparison

BAU schools will not receive the intervention (MHWC role or training program). They will complete T1, T2, T3, T5 and T6 surveys (see Table 2).

**Table 2 Tab2:** Summary of outcomes and measures

Outcome	Variable	Data source/Measure	Participant group						Data collection timepoint					
			MHWC	Trainee	School staff (INT)	School staff (BAU)	Years 2 / 4 Teachers	Years 2 / 4 Parents	T1	T2	T3	T4	T5	T6
Primary Outcome	Confidence to support student mental health and wellbeing	School Mental Health Self-efficacy Teacher Survey [44]	✔	✔	✔	✔			✔				✔	✔
Secondary Outcome	Perceived levels of support in managing child mental health	Study designed	✔	✔	✔	✔		✔	✔				✔	✔
	Mental health literacy	Child Health Poll [45] Study designed perceived confidence and skills Vignettes	✔	✔	✔	✔		✔	✔				✔	✔
	Child mental health stigma	The Attitudes about Child Mental Health Questionnaire [46]	✔	✔	✔	✔		✔	✔				✔	✔
	Student mental health and wellbeing	Strengths & Difficulties Questionnaire [47] Attitude to Schools Survey [48] and Parent Opinion Survey [49]					✔	✔		✔	✔		✔	✔
	Levels of engagement with DET-based and externally based mental health and wellbeing services	Study designed Attitude to Schools Survey [48] and Parent Opinion Survey [49]	✔	✔	✔	✔		✔	✔	✔			✔	✔
	Prioritisation of child mental health & wellbeing within school’s curriculum & planning	Study designed	✔	✔	✔	✔		✔	✔				✔	✔
	School engagement and perceived mental health support	Attitude to Schools Survey [48], Parent Opinion Survey [49] and study designed	✔	✔	✔	✔		✔	✔				✔	✔
	Level of unmet mental health and wellbeing need within classrooms	Study designed			✔	✔			✔				✔	✔
Process Outcomes	Implementation (feasibility, acceptability, appropriateness, reach, fidelity)	Acceptability of Intervention Measure, Intervention Appropriateness Measure & Feasibility of Intervention Measure [50] Focus Groups	✔	✔	✔								✔	
	Levels of engagement with MHWC	Study designed and Focus Groups	✔	✔	✔		✔					✔	✔	
	Cost	Cost inputs (time, resources, Casual Relief Teacher funding) Data will be obtained from referral activities log, job analysis, focus groups and surveys	✔						✔			✔	✔	
Moderators	Readiness to implement	Readiness to Implement scale [51]	✔	✔	✔				✔					
	MHWC Time allocation	FTE allocation; study devised measures	✔						✔			✔	✔	
	School & Participant Characteristics	Demographics	✔	✔	✔			✔	✔	✔				

## Primary and secondary outcomes and measures

### School and participant characteristics

#### School characteristics

Information will be collected for each school including the Index of Community Socio-Educational Advantage (ICSEA) [54] metropolitan, regional, rural or remote location as determined by DET, number of enrolments and region (NW or SW).

#### Participant demographic characteristics and professional experience

Basic demographic information will be collected via survey, including participant age, school postcode, highest level of education, languages spoken at home, the number of years teaching and/or working within primary schools (school staff only), previous participation in child mental health and wellbeing related training courses and professional development (school staff only).

### Primary outcome and measure

#### Teacher confidence in supporting mental health

The School Mental Health Self-Efficacy Teacher Survey (SMH-SETS) [44] will be completed by classroom teachers. The SMH-SETS is a psychometrically sound 15 item measure that utilises a 6-point Likert scale that addresses teacher’s confidence in their ability to successfully support students’ mental health with excellent internal consistency (Cronbach’s alpha = .91), item reliability and validity [55].

### Secondary outcomes and measures

#### Perceived level of support for student mental health

To evaluate the impact of the MHWC model on perceived levels of support for student mental health, study designed questions will be developed to capture (a) *how much support staff expect* in managing student mental health and wellbeing from within their school and DET, and (b) *how supported staff have felt in the past month* from within their school and DET.

#### Mental health literacy

To evaluate the perceived level of knowledge and confidence in identifying child mental health and wellbeing issues, study designed items will be developed and rated on a 6-point Likert scale from strongly agree to strongly disagree. Study devised multiple choice items requiring respondents to choose the correct answer will also be developed to capture knowledge about internalising and externalising mental health issues in students.

To evaluate skills and confidence related to mental health and wellbeing of students, school staff will complete a skills assessment at T1, T5 and T6 (see Table 2). The skills assessment will comprise case study vignettes covering a range of potential scenarios school staff may be presented with, and respondents will be asked about key behavioural issues, contributing factors, strategies and further support required, as well as confidence in supporting the child described in the vignette.

To evaluate parents/carers child mental health literacy, items will be drawn from the Child Health Poll – child mental health edition [45]. The Child Health Poll includes items that address parent confidence in recognising and managing child mental health issues (measured on a 3-point Likert scale: confident, somewhat confident, not confident) and items that address knowledge about child mental health (measured on a 6-point Likert scale: strongly agree to strongly disagree).

#### Child mental health stigma

To evaluate changes in attitudes and stigma the Attitudes about Child Mental Health Questionnaire (ACMHQ [46];) will be administered. It consists of 30 items with four subscales: child dangerousness/incompetence, general stereotypes, community devaluation/discrimination and personal attitudes. Each item is rated on a 6-point Likert response scale that ranges from 1 (strongly disagree) to 6 (strongly agree). The ACMHQ subscales have good to excellent internal consistency (α =0.78–0.96) [46].

#### Unmet mental health and wellbeing need

To evaluate changes in the level of unmet need for mental health and wellbeing support within school classrooms, study devised questions will be used to capture (a) the proportion of students within each teacher’s classroom who have unmet needs for school-based mental health and wellbeing support and (b) the barriers to obtaining mental health and wellbeing support for these students.

#### Child mental health and wellbeing

To evaluate the impact of the MHWC model on child mental health, the Strength and Difficulties Questionnaire (SDQ) will be used [47]. The 25-item measure is a brief emotional and behavioural screening questionnaire for children aged 4–10 years old. There are 5 subscales with 5 items in each; emotional symptoms, conduct problems, hyperactivity/inattention, peer relationships and prosocial behaviour. The SDQ has good concurrent and predictive validity, and satisfactory internal consistency [47].

#### Prioritisation of student mental health

To evaluate the level of prioritisation of child mental health and wellbeing, school leaders will answer questions exploring the level of priority given to wellbeing and mental health provision for students, whether wellbeing and mental health provision for students is part of the school strategic plan or annual implementation plan, or if the school has a policy related to child mental health and wellbeing.

#### Engagement with mental health support

School staff engagement with school-based and external child mental health services will be measured using study designed questions to capture the perceived level of engagement required, the actual level of engagement and the types of child mental health support and services provided to staff.

Student engagement with mental health support and perceived availability of mental health and wellbeing support will be measured using subscales from the Attitudes to School Survey (AToSS) years 4–6 version [48]. The AToSS is a DET administered survey that will be completed by students and consists of 60 items across 6 domains with 3–5 factors/subscales within each domain. The following subscales will be used: Teacher concern; School connectedness; Advocate at school; Managing bullying; Peer relationships; Perceptions of school; Social outcomes; Subjective physical & mental health; Experience of COVID-19. The survey items use a five-point Likert scale from 1 (strongly disagree) to 5 (strongly agree).

Parent engagement with school-based and external child mental health and wellbeing support will be measured using study designed items and items from the DET Parent Opinion Survey (POS) [49]. The following subscales from the POS will be used: Student agency and voice; Confidence & resiliency skills; Managing bullying; Promoting positive behaviour; School connectedness; Positive transitions; Remote & Flexible learning items (2020). The items use a five-point Likert scale from 1 (strongly disagree) to 5 (strongly agree).

### Implementation measures

#### Readiness to implement

To effectively evaluate the implementation of the MHWC model we will also seek to understand individual and contextual characteristics (across all participant groups) that are present prior to implementation which may also influence program outcomes. We will use the Readiness to Implement Scale [51] which looks at three key areas: feasibility, fit and staff support. It is a self-report measure, consisting of 20 items and has an overall reliability of Cronbach’s alpha [α] = .92 [51].

#### Costs of the intervention

Costs of delivering the intervention will be estimated to inform wider implementation. This will be based on budgets for each role, the log of activities kept by MHWCs tracking time and resources used and from records of replacement teachers filling in for classroom teachers to attend professional development and training activities run by the MHWCs. The costs will be from the perspective of the school.

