#### MHWC referral activities log and job analysis

To evaluate the tasks, responsibilities, time, and resources required to achieve all aspects of the MHWC role and successful implementation of the MHWC model, MHWC activity will be recorded in a study developed database. This information will include number of students impacted, number of interactions with classroom teachers, time spent on tasks, type of mental health and wellbeing activities the MHWC is assisting with, number of referrals made, uptake/outcome of referral, waitlist times, number, and type of interactions with regional staff. This information will be collected for two working weeks during the academic school year (Semester 2).

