### Cost analysis

Variation in costs across participating schools will be evaluated to identify factors that may impact on the costs of delivering the intervention according to school characteristics such as number of student enrolments, location, and SES. Based on these estimated costs, budget impact of delivering the intervention state-wide will be calculated, with associated resource implications, particularly workforce.

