Second, standardised measures and data collection methods for some of the project outcomes were not available (i.e., Mental Health Literacy [62], routine collection of outcomes (e.g. referral data)). Ideally standardised measures and data collection processes would be used to maximise the quality of the research conclusions, including comparisons with previous school-based mental health initiatives, and across intervention and BAU schools. This lack of measures relevant to the study outcomes and standardised processes for routine data collection in schools likely reflects a historical lack of scientific rigour in evaluating school-based initiatives [63]. To mitigate the lack of appropriate measures, the research team in collaboration with an expert advisory panel, developed bespoke items to target these outcomes. The measures developed for this project will likely be relevant for future projects and therefore measures development may form a sub-project of the broader study. To mitigate the lack of standardised, routine data collection across schools, the research team has developed data collection templates that will capture pertinent referral pathway information for students. Due to the absence of routinely collected resource or cost data on mental health supports in schools, it is not possible in this study to compare the costs in intervention and BAU schools, so the full cost implications of the model will not be estimated, nor will an economic evaluation that compares costs and outcomes between intervention and BAU schools be conducted.

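### The state-wide budget impact is built on school-perspective costs that do not capture delivery of the training program, so as written it would be biased downward

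*Protocol article*

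**What the plan says.** Under Costs of the intervention, the aim is stated as "Costs of delivering the intervention will be estimated to inform wider implementation". Three sources are named: the budget for each role, the log in which coordinators record time and resources, and records of "replacement teachers filling in for classroom teachers to attend professional development and training activities run by the MHWCs". The section then fixes the viewpoint: "The costs will be from the perspective of the school".

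Under Cost analysis, the estimated costs are examined for variation across schools. On the basis of those same costs, "budget impact of delivering the intervention state-wide will be calculated", together with resource implications, workforce in particular.

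The Intervention section under Procedure defines the intervention as two things, the coordinator role and the training program. The MHWC training program section describes the second as a "purpose designed training program, delivered by the research team". It has a three-day synchronous online core (induction and three modules), asynchronous material, and Communities of Practice sessions with a selected expert at each. Three further staff per intervention school are nominated to attend parts of it.

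The Cost row of Table 2 lists time, resources and Casual Relief Teacher funding as inputs. It adds: "Data will be obtained from referral activities log, job analysis, focus groups and surveys". Only the coordinator group is ticked.

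**The concern.** A budget impact tells a payer what a roll-out would cost that payer. Here the payer for a state-wide roll-out would be the education department, but the costs are collected from the viewpoint of the single school. Training provided to schools by another body is not a cost to the school, although someone must pay for it if the model is extended. The figure would then cover the coordinators without the program that trains them.

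The Discussion says the results will inform mental health service reform and possible state and national roll-out. A figure missing one of the intervention's two components would make the model look cheaper than it is. The trainers would also drop out of the workforce implications that the article promises.

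**Working it through.** The article reports no cost figure, so there is none to reproduce. The check compares what the intervention contains with what the costing captures.

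**Step 1. Match each component to a source.**

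| Component (Intervention; MHWC training program) | Source named under Costs of the intervention or in Table 2 | Captured? |
|---|---|---|
| Coordinator role | Role budgets; activity log | Yes |
| Relief while classroom teachers attend coordinator-run activities | Replacement-teacher records | Yes |
| Trainers and online delivery of the core program | None | No; also outside a school viewpoint |
| Experts at Communities of Practice sessions | None | No; also outside a school viewpoint |
| Relief while nominated staff attend the core training | Replacement-teacher records cover coordinator-run activities only; Table 2 names relief funding without restriction | Not clear |

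**Step 2. Follow the costs forward.** The Cost analysis section takes these estimated costs as its base. No passage adds training delivery or changes the viewpoint before scaling to the state.

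**Step 3. Bound the nominated-staff time.** Inputs: 16 intervention schools, 3 nominated staff per school (Table 1 gives 48), and a 3-day core program.

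- 16 x 3 = 48 staff
- 48 x 3 = 144 person-days

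This is a ceiling, because nominated staff attend only components of the training and some may be leaders or wellbeing staff who need no replacement.

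**Step 4. Direction and possible size.** Let C be the school-perspective cost and s x C the omitted cost of training delivery. The complete cost is C(1 + s), so the stated figure falls short of it by the fraction s/(1 + s). The document gives no value for s; these values are assumptions.

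| Assumed s | Shortfall s/(1 + s) |
|---|---|
| 0.02 | 0.02/1.02 = 2.0% |
| 0.05 | 0.05/1.05 = 4.8% |
| 0.10 | 0.10/1.10 = 9.1% |
| 0.20 | 0.20/1.20 = 16.7% |
| 0.30 | 0.30/1.30 = 23.1% |

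For any s above zero the figure is too low. The range is illustrative and not an estimate.

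**The case against.** The best defence is that the exclusion is inferred. The article says it will cost delivery of the intervention, and it defines the intervention as including the training. Role budgets could be read to cover trainers. The school viewpoint may not be a strict who-pays rule either, since the coordinator post is funded on an enrolment scale that suggests outside money and its budget is still counted. Itemised cost lists are also commonly left to a fuller document.

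Part of this stands: the article never says outright that training delivery is left out. But the only role it defines and funds is the coordinator, which it lists separately from the training. If trainers were meant, that would conflict with the stated viewpoint. The point is not missing detail, because viewpoint, sources and use are all stated and do not fit together.

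A second defence is the Discussion's caveat that full cost implications will not be estimated. Its reason is the lack of routine data: "it is not possible in this study to compare the costs in intervention and BAU schools". That concerns the contrast with control schools. It mentions neither training cost nor viewpoint, and the state-wide figure is still promised.

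A reader might also infer several stronger points that the document does not support:

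- **Table 2 conflicts with the log.** The Cost row is ticked at T1, T4 and T5, while the log runs for two weeks in Semester 2. The row names four data sources, so its ticks need not mean log data at each timepoint.
- **Two log weeks are scaled up to a year.** No passage says so, and role budgets need no such extrapolation.
- **Coordinators' own training days go uncounted.** The coordinator is an additional, funded post, so this time plausibly sits inside the role budget. Adding it risks double counting.
- **The regional and rural loading is left out.** It is described with the coordinator's funding, and nothing shows that role budgets exclude it.

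**Conclusion.** The point holds in a limited form. The stated viewpoint and sources do not capture delivery of the training program, and the state-wide budget impact rests on those costs alone. Followed as written, the figure would be biased downward. This assumes that role budgets mean the coordinator role and that training delivery has a positive cost in a roll-out.

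A reader might want to attach a percentage, or to treat the 144 person-days as an established omission. The document supports neither. It contains no costs, and the nominated-staff time is an upper bound on something that is unclear, not plainly excluded. The issue does not touch the primary outcome or any effectiveness analysis; it matters for the roll-out decision that the costing is meant to inform.

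**What to change.** In Cost analysis, calculate the state-wide budget impact from the perspective of the education department as funder, and keep the school perspective as a secondary view. To the costs already listed, add:

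- recurrent training delivery: trainers, Communities of Practice experts and online delivery;
- relief for nominated staff attending the core training, based on days actually attended and replaced;
- one-off development of the training, on a separate line so that it is not scaled with the number of schools.

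In Costs of the intervention, say which viewpoint serves which purpose. If training delivery cannot be costed, label the state-wide figure as excluding it wherever it is reported.

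The cost of the change is a few extra cost lines, a record of trainee relief and some rewording. The downside is a less favourable budget figure.
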